- For subjects with existing chronic mild hepatic impairment (Child-Pugh class A) at enrollment, the starting dose has to be adjusted to a level of 280 mg daily (two capsules).
- For subjects who develop mild hepatic impairment while on study (Child-Pugh class A), the recommended dose reduction for ibrutinib/placebo is to a level of 280 mg daily (two capsules) unless lower doses had already been implemented.
- For subjects who develop moderate hepatic impairment while on study (Child-Pugh class B), the recommended dose reduction is to a level of 140 mg daily (one capsule).
  1. Overdose
- Subjects who develop severe hepatic impairment (Child-Pugh class C) must hold study drug until resolved to moderate impairment (Child-Pugh class B) or better.

Subjects who develop acute hepatic toxicity with liver enzymes Grade 3 or higher while on study should be managed per standard dose modification guidelines in Section 8.

There is no specific experience in the management of ibrutinib overdose in patients. No maximum tolerated dose (MTD) was reached in the Phase 1 study in which subjects received up to 12.5 mg/kg/day (1400 mg/day). Healthy subjects were exposed up to single dose of 1680 mg. One healthy subject experienced reversible Grade 4 hepatic enzyme increases (AST and ALT) after a dose of 1680 mg. Subjects who ingest more than the recommended dosage should be closely monitored and given appropriate supportive treatment.

Refer to Section 10.0 for further information regarding AE reporting.

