| Injury, poisoning and | **Infusion-related Reaction** | | |
| procedural complications | Grade ≥3 | Discontinue and enter Event Monitoring | Discontinue and enter Event Monitoring |
| Investigations | **Neutrophil count decreased (See also Blood and lymphatic systems disorders/Febrile neutropenia)** | | |
|  | Grade ≥3 neutropenia with  infection or  Grade 4 neutropenia | *Hold until ≤Grade 2 Discontinue if does not resolve to ≤Grade 2 within 12 weeks  after last dose administration, and enter Event Monitoring. | Hold until ≤Grade 1 or baseline  Resume at the next lower dose level (if occurs at 140 mg once  daily, discontinue). |
|  | **Platelet count decreased** | | |
|  | Platelet counts <25 x 10^9^/L or platelet counts <50 x 10^9^/L with clinically significant bleeding events | *Hold until ≤Grade 2 Discontinue if does not resolve to ≤Grade 2 within 12 weeks  after last dose administration, and enter Event Monitoring | Hold until ≤Grade 1 or baseline  Resume at the next lower dose  level (if occurs at 140 mg once daily, discontinue). |
| Renal and urinary disorders | **Acute kidney injury** | | |
|  | Nephritis Grade 2 | *Hold until symptoms resolved to ≤Grade 1, initiate systemic steroids (see 9.6). Discontinue if does not resolve to ≤Grade 1 within 12 weeks after last dose administration, and enter Event Monitoring | Hold until pembrolizumab is resumed  Resume at the next lower dose level (if occurs at 140 mg once daily, discontinue).  Discontinue if pembrolizumab is discontinued, and enter  Event Monitoring |
|  | Grade ≥3 | Discontinue and enter Event Monitoring | Discontinue and enter Event Monitoring |
| Respiratory, thoracic, and mediastinal disorders | **Pneumonitis** | | |
|  | Grade 2 | *Hold until symptoms resolved to ≤Grade 1, initiate systemic steroids  Discontinue if does not resolve to ≤Grade 1 within 12 weeks after last dose administration, and enter Event Monitoring | Hold until pembrolizumab resumed  Resume at the next lower dose level (if occurs at 140 mg once daily, discontinue).  Discontinue if pembrolizumab is discontinued, and enter Event Monitoring |
|  | Grade ≥3 | Discontinue and enter Event Monitoring | Discontinue and enter Event Monitoring |
| Skin and subcutaneous tissue disorders | **Rash maculo-papular** | | |

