|  | Grade 2 | *Hold pembrolizumab until resolves to ≤Grade 1 Discontinue if does not resolve to ≤Grade 1 within 12 weeks after last dose administration | Hold until pembrolizumab is resumed  Resume at the next lower dose level (if occurs at 140 mg once daily, discontinue).  Discontinue if pembrolizumab  is discontinued, and enter Event Monitoring |

| **System/Organ/Class (SOC)** | **ADVERSE EVENTS/SYMPTOMS** | **ACTIONS** | |
| --- | --- | --- | --- |
|  |  | **Pembrolizumab** | **Ibrutinib** |
|  | Grade ≥3 | Hold pembrolizumab. If resolves to ≤Grade 1 within 72 hours resume treatment  If not, discontinue and enter Event Monitoring | Hold until pembrolizumab resumed  Resume at the next lower dose level (if occurs at 140 mg once daily, discontinue).  Discontinue if pembrolizumab is discontinued, and enter Event Monitoring |
| Other non-laboratory Adverse Events |  | | |
|  | Grade 3 | *Hold pembrolizumab until resolves to ≤Grade 1 Discontinue if does not resolve to ≤Grade 1 within 12 weeks after last dose administration | Hold until pembrolizumab resumed Resume at the next lower dose level (if occurs at 140 mg once daily, discontinue).  Discontinue if pembrolizumab is discontinued, and enter Event Monitoring |
|  | Grade 4 | Discontinue and enter Event Monitoring | Discontinue and enter Event Monitoring |

*If ibrutinib is discontinued according to Table 8.2, continue pembrolizumab until disease progression or intolerance develops or patient refusal.

- 1. Modifications Based on Concomitant Medications and Procedures for Ibrutinib
     - **Dose Modifications for Use with CYP3A Inhibitors and Inducers**

Ibrutinib is metabolized primarily by CYP3A. Avoid co-administration with strong CYP3A4 or moderate CYP3A inhibitors and consider alternative agents with less CYP3A inhibition.

- - - - If a strong CYP3A inhibitor (eg, ketoconazole, posaconazole, indinavir, nelfinavir, ritonavir, saquinavir, clarithromycin, telithromycin, itraconazole, nefazadone, or cobicistat) must be used, reduce ibrutinib to 140 mg for the duration of the inhibitor or withhold ibrutinib treatment temporarilty (for 7 days or less). Pembrolizumab may be continued at current dose. If unable to discontinue strong CYP3A inhibitor use within 12 weeks then permanently discontinue ibrutinib.

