# Ancillary Treatment/Supportive Care

- 1. Full supportive care

Patients should receive full supportive care while on this study. This includes blood product support, antibiotic treatment, and treatment of other newly diagnosed or concurrent medical conditions. All blood products and concomitant medications such as antidiarrheals, analgesics, and/or antiemetics received from the first day of study treatment administration until 28 days after the final dose will be recorded in the medical records.

- 1. Hypersensitivity reactions

Patients do not require premedication prior to ibrutinib or Pembrolizumab treatment, as hypersensitivity reactions is not expected. In the unlikely event of a hypersensitivity reaction, treatment with antihistamines, H2 blockers, and corticosteroids is recommended. Patients should be pre-medicated with the typical regimen for subsequent cycles.

- 1. Concurrent enrollment in other trials

Patients may not enroll in a different clinical study, including Cancer Control studies, in which investigational procedures or agents are being used, while participating in this study.

- 1. Palliative radiation

Patients must terminate study treatment if they are to receive radiation therapy for palliative reasons as it impacts upon assessing response.

- 1. General patient monitoring and supportive care guidelines
  2. Patients should be carefully monitored during the treatment phase and then followed appropriately. Decisions for retreatment or dose modifications/interruption should follow the guidelines in Sections 8.2.
  3. Patients who have an ongoing study agent-related serious adverse event upon study completion or at discontinuation from the study will be contacted by the treating physician or his/her designee at least every 2 weeks until the event is resolved or determined to be irreversible.
  4. Side effect management for **PEMBROLIZUMAB** toxicities

These are to be regarded as guidelines for managing toxicity that occurs with pembrolizumab therapy and should not replace clinical judgement (i.e. - patients with Trade 1 rash may require systemic steroids).

- 1. Diarrhea

9.611 Grade 1- without abdominal pain/or blood in stool and symptoms, may be caused either by pembrolizumab or by ibrutinib. Infectious etiologies should be ruled out. Patients may be managed symptomatically, including the use of loperamide. Instruct patients to report any increase in stools.

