[http://www.fda.gov/downloads/AboutFDA/ReportsManualsForms/Forms/UCM0](http://www.fda.gov/downloads/AboutFDA/ReportsManualsForms/Forms/UCM048334.pdf) [48334.pdf](http://www.fda.gov/downloads/AboutFDA/ReportsManualsForms/Forms/UCM048334.pdf)

or [http://www.fda.gov/AboutFDA/ReportsManualsForms/Forms/ListFormsAlphabe](http://www.fda.gov/AboutFDA/ReportsManualsForms/Forms/ListFormsAlphabetically/default.htm)

[tically/default.htm](http://www.fda.gov/AboutFDA/ReportsManualsForms/Forms/ListFormsAlphabetically/default.htm)

Instructions for completing the MedWatch 3500A: [http://www.fda.gov/downloads/Safety/MedWatch/HowToReport/DownloadFor](http://www.fda.gov/downloads/Safety/MedWatch/HowToReport/DownloadForms/UCM387002.pdf) [ms/UCM387002.pdf](http://www.fda.gov/downloads/Safety/MedWatch/HowToReport/DownloadForms/UCM387002.pdf)

- 1. **EXPECTED Serious Adverse Events: Protocol Specific Exceptions to Expedited Reporting**

For this protocol only, the following Adverse Events/Grades are expected to occur within this population and do not require Expedited Reporting. These events must still be reported via Routine Reporting (see Section 10.6).*

*Report any clinically important increase in the rate of a serious suspected adverse reaction (at your study site) over that which is listed in the protocol or investigator brochure as an expedited event.

*Report an expected event that is greater in severity or specificity than expected as an expedited event.

| **System Organ Class**  **(SOC)** | **Adverse event/ Symptoms** | **CTCAE Grade at which the event**  **will not be expeditedly reported^1^** |
| --- | --- | --- |
| Blood and lymphatic system disorders | Anemia | ≤Grade 3 |
|  | Febrile neutropenia | ≤Grade 3 |
| Cardiac Disorders | Myocardial infarction | ≤Grade 3 |
| Endocrine disorders | Hypothyroidism | ≤Grade 3 |
|  | Hyperthyroidism | ≤Grade 3 |
|  | Hypophysitis | ≤Grade 3 |
| Gastrointestinal disorders | Nausea | ≤Grade 3 |
|  | Vomiting | ≤Grade 3 |
|  | Gastric hemorrhage | ≤Grade 3 |
|  | Abdominal pain | ≤Grade 3 |
|  | Diarrhea | ≤Grade 3 |
|  | Hepatitis | ≤Grade 3 |
| General disorders and  administrations site conditions | Fatigue | ≤Grade 3 |
|  | Fever | ≤Grade 3 |
| Immune system disorders | Allergic reaction/anaphylaxis | ≤Grade 3 |
| Injury, poisoning, and procedural complications | Wound dehiscence | ≤Grade 3 |
| Investigations | Neutrophil count decreased | ≤Grade 4 |
|  | Platelet count decreased | ≤Grade 3 |

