16.71 Safety Stopping rules

Dose limiting toxicities and other acute adverse events will be monitored by the study team on a monthly basis. If during the course of enrolling the first 6 patients on trial, 2 patients develop a grade 3+ maculo-papular rash, pneumonitis, nephritis, fever, allergic reaction, anaphylaxis, dyspnea, or increased blood bilirubin or grade 4 hyperthyroidism, hypophysitis or diarrhea, which are considered possibly, probably, or definitely related to treatment, any time during treatment enrollment will be temporarily closed.

Any time after the first 6 patients have been enrolled, if 30% or more of the patient enrolled develop one (or more) of the toxicities listed in the table below during treatment or within 30 days of discontinuing protocol treatment and the toxicity is considered to be possibly, probably, or definitely related to treatment, enrollment will be temporarily closed.

| **Toxicity** | **Severity/duration** |
| --- | --- |
| Neurologic | Grade 2 and not resolved to ≤ Grade 1 within 14 days  ≥ Grade 3 regardless of time to resolution |
| Hematologic | Grade 4 and not resolved to ≤ Grade 1 within 14 days  Grade 3 with Grade 3+ febrile neutropenia or hemorrhage, regardless of time to resolution |
| Other | Grade 3 and not resolved to ≤ Grade 1 within 14 days  Grade 4 regardless of time to resolution  Any toxicity that leads to treatment discontinuation due to toxicity |

- 1. Inclusion of Women and Minorities

| **Accrual Targets** | | | |
| --- | --- | --- | --- |
| **Ethnic Category** | **Sex/Gender** | | |
|  | **Females** | **Males** | **Total** |
| Hispanic or Latino | 0 | 1 | 1 |
| Not Hispanic or Latino | 10 | 12 | 22 |
| **Ethnic Category: Total of all subjects*** | **10** | **13** | **23** |
| **Racial Category** | | | |
| American Indian or Alaskan Native |  |  |  |
| Asian |  |  |  |
| Black or African American |  |  |  |
| Native Hawaiian or other Pacific Islander |  |  |  |
| White | 10 | 13 | 23 |
| **Racial Category: Total of all subjects*** | **10** | **13** | **23** |

| **Ethnic Categories:** | **Hispanic or Latino –** a person of Cuban, Mexican, Puerto Rican, South or Central American, or other Spanish culture or origin, regardless of race. The term “Spanish origin” can also be used in addition to “Hispanic or Latino.”  **Not Hispanic or Latino** |
| --- | --- |

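### Sections 8.2 and 9.2 do not give one instruction on further treatment after a Grade 3 hypersensitivity reaction during a pembrolizumab infusion

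*Protocol*

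**What the plan says.** Table 8.2 (Section 8.2) has a row for infusion-related reaction. Up to the pembrolizumab column it reads "procedural complications | Grade ≥3 | Discontinue and enter Event Monitoring", and the ibrutinib column gives the same action.

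Section 9.2 covers hypersensitivity to either drug. It calls such reactions unexpected and then gives two instructions: "In the unlikely event of a hypersensitivity reaction, treatment with antihistamines, H2 blockers, and corticosteroids is recommended" and "Patients should be pre-medicated with the typical regimen for subsequent cycles". Neither names a grade, and neither points to Table 8.2.

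Section 9.5 does point there: "Decisions for retreatment or dose modifications/interruption should follow the guidelines in Sections 8.2".

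Allergic reaction and anaphylaxis are working terms elsewhere. Section 10.32 lists "Allergic reaction/anaphylaxis | ≤Grade 3" among the exceptions to expedited reporting, under Immune system disorders. Section 10.6 grades both terms at each evaluation, under the same class. The first safety closure rule in Section 16.71 names "allergic reaction, anaphylaxis, dyspnea, or increased blood bilirubin". Table 8.2 has no row for either term.

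**The concern.** Whether a patient is re-exposed after a severe reaction is a safety decision, and sites should find one answer to it. Here the answer can change with the adverse event term chosen and the section consulted, so two sites could handle the same event differently and both be following the protocol.

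There is a smaller consequence for monitoring. One limb of the closure rule in Section 16.71 counts toxicities that lead to stopping treatment, so the same ambiguity can decide whether an event is counted.

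**Working it through.** No power, sample size or event count is involved, so the check is a comparison of the text. Take a Grade 3 hypersensitivity reaction during a pembrolizumab infusion, judged at least possibly related (Table 8.2 applies only to related events).

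| Place read | Pembrolizumab | Ibrutinib |
| --- | --- | --- |
| Table 8.2, infusion-related reaction, Grade ≥3 | Stop | Stop |
| Table 8.2, Immune System Disorders, immune-related, Grade ≥3 (gastrointestinal and endocrine excepted) | Stop | Stop |
| Table 8.2, Other non-laboratory, Grade 3 | Hold, then resume on recovery | Hold, then resume one level lower |
| Section 9.2 read alone | Later cycles with pre-medication | Not distinguished |

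1. **The catch-all row.** For pembrolizumab it reads "Hold pembrolizumab until resolves to ≤Grade 1 Discontinue if does not resolve to ≤Grade 1 within 12 weeks after last dose administration". Ibrutinib waits for pembrolizumab to resume and restarts one level lower. It is stopped if the event arose at 140 mg or if pembrolizumab is stopped.

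2. **Which row applies to allergic reaction or anaphylaxis.** The table does not say. The immune row is a candidate because Sections 10.32 and 10.6 place the terms in that class. The catch-all row is a candidate because no row names them. At Grade 3 the two rows give opposite actions.

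3. **Grade 4.** The infusion-reaction row, the immune-related row and the catch-all Grade 4 row all stop both drugs. The table is therefore consistent at Grade 4, and only Section 9.2 read alone differs. The ambiguity between rows is confined to Grade 3.

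4. **Force of the table.** Section 8 makes the table strict in Cycle 1 and a guideline afterwards. Section 7 gives pembrolizumab once in Cycle 1, on Day 8, and then on Day 1 of each later cycle. Every infusion after the first thus falls where the table is guidance.

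5. **The tie-break in Section 8.** The instruction to apply the greatest reduction concerns several adverse events at once. It does not address one event that fits more than one row.

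6. **Closure rule in Section 16.71.** The first limb covers the first 6 patients on trial. By Amendment 6, 2 + 11 = 13 had been enrolled, so the later limb is the relevant one. It closes enrolment temporarily at 30% or more of patients enrolled. For toxicities classed as Other it counts Grade 3 events unresolved after 14 days, all Grade 4 events, and any toxicity that leads to stopping treatment. A Grade 3 reaction that settles to Grade 1 or lower within 14 days therefore counts only if treatment was stopped. It counts under the immune or infusion row, and not under the catch-all row if treatment resumes.

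7. **Weight of one such event.** With the planned maximum of 23 patients, 0.30 × 23 = 6.9, so 7 patients trigger closure and one patient adds 1/23 = 4.3%. If only the 16 at the maximum tolerated dose are counted, 0.30 × 16 = 4.8, so 5 trigger it and one adds 1/16 = 6.3%.

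**The case against.** The strongest reply is Section 9.5. It makes Section 8.2 the authority on retreatment, so Section 9.2 can be read as supportive care for patients who stay on treatment under the table. On that reading there is no flat contradiction between Sections 8.2 and 9.2, and a reader who infers one goes further than the text allows. What Section 9.5 does not do is settle the outcome: it refers the site to a table that gives these terms no row and that is only a guideline after Cycle 1.

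A reader might also infer that a Grade 3 allergic reaction belongs in the hold-and-resume row. The protocol does not say so. The immune-related row is at least as good a candidate, and it agrees with the infusion-reaction row.

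Nor are the terms always one event. Section 9.2 also covers an oral drug, and the rash paragraph of Section 15 describes ibrutinib hypersensitivity as erythema, urticaria and angioedema, which need not be infusion reactions. Different actions for different events are not an inconsistency. The overlap is real only for a reaction during the pembrolizumab infusion.

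Finally, the trial consequences are limited. In Cycle 1, Section 7 makes other non-hematologic toxicity of Grade 3 or higher dose-limiting whichever of these terms is used. Section 16 keeps all eligible treated patients in the analysis.

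**Conclusion.** The point stands as an internal inconsistency of wording with a narrow scope. For a Grade 3 hypersensitivity reaction during a pembrolizumab infusion, the protocol supports stopping both drugs, holding and resuming, or (from Section 9.2 alone) continuing with pre-medication. The term and section used decide which.

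This rests on two readings: that such a reaction may reasonably be coded as either infusion-related or allergic, and that no unseen coding instruction assigns the terms to a row. The documents give no rate of severe reactions for this combination, so no probability is attached.

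The effect on the closure rule is at most whether one patient is counted per such event. A reader might infer a threat to the expansion cohort's sample size or its two-responses-in-14 rule; nothing in the documents shows one. The case for acting is that the decision concerns re-exposure after a severe reaction and the correction is small.

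**What to change.** Reconcile the passages in the next amendment:

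- In Section 9.2, state the grades to which pre-medication and further cycles apply, and add a cross-reference to Table 8.2.
- In Table 8.2, assign allergic reaction and anaphylaxis to one named row, so that a given grade leads to one instruction whichever term is recorded.

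The clinical team sets the action; this review takes no position on which is right. The cost is two short wording changes, with no extra patients, visits or procedures and no change to the statistical design.

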As the current standard of care for metastatic melanoma, pembrolizumab is well-tolerated at 200mg/3 weeks with an acceptable adverse effects profile. Based on currently available data, ibrutinib has an acceptable safety profile as monotherapy and when combined with chemoimmunotherapy or immunotherapy. No MTD was reached in the Phase 1 study in which subjects received intermittent dosing up to 12.5 mg/kg/day (1400mg) and continuous dosing of 560 mg or with combination therapies (up to 560 mg). Based on the above safety evidence, ibrutinib 560mg continuous dosing in combination with pembrolizumab 200 mg/3 weeks was initially tested. Both of the first two patients enrolled experienced Grade 3 skin rash within a week of the first dose of pembrolizumab. This level of severity and incidence has not been observed in other malignancies treated with ibrutinib or pembrolizumab, We suspect that this is a result of immunomodulation from the combination therapy in the setting of the unique tumor microenviornent of metastatic melanoma. Based on this observation, we modified this protocol to a phase I study with an expansion cohort to find the maximum tolerated dose of ibrutinib in combination of pembrolizumab. In brief, we will use a 3+3 Phase I design with a starting dose for ibrutinib at 280 mg.

As metabolism of Ibrutinib is liver dependent, lower doses are needed for patients with pre- exsiting clinically significant liver impairment. Given the lower starting doses we have selected, the decision was made to exclude patients with pre-exsiting clinically significant liver impairment.

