# Dosage Modification Based on Adverse Events

Strictly follow the modifications in this table for the first cycle, until individual treatment tolerance can be ascertained. Thereafter, these modifications should be regarded as guidelines to produce mild-to-moderate, but not debilitating, side effects. If multiple adverse events are seen, administer dose based on greatest reduction required for any single adverse event observed. Reductions or increases apply to treatment given in the preceding cycle and are based on adverse events observed since the prior dose.

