|  | Grade 4 | Discontinue and enter Event Monitoring  Initiate systemic steroid treatment (see Section 9.6) | Discontinue and enter Event Monitoring |
|  | **Nausea and Vomiting** | | |
|  | Grade ≥3 despite optimal  anti-emetic therapy | Continue if Grade 3  Hold if >Grade 3 until resolves  to ≤Grade 1 | Hold  Resume according to Table 8.2 |
| Investigations | Hepatic Dysfunction (**AST** or **ALT** or total **bilirubin**) and immune-mediated hepatitis | | |
|  | Grade 2  (AST or ALT >3 × and  <5 × ULN  or total bilirubin >1.5 × and <3 × ULN) | *Hold until levels resolve to  ≤Grade 1  (AST or ALT ≤3× ULN,  total bilirubin ≤1.5 × ULN)  Consider initiating systemic steroid treatment (see Section 9.6)  Discontinue if does not resolve to ≤Grade 1 within 12 weeks after last dose administration,  and enter Event Monitoring | Hold until pembrolizumab resumed  Resume at the next lower dose level (if occurs at 140 mg once daily, discontinue).  Discontinue if pembrolizumab is discontinued, and enter Event Monitoring |
|  | Grade 3  (AST or ALT >5 × ULN or  total bilirubin >3 ×ULN) or for patients with liver metastasis who begin treatment with Grade 2 AST or ALT, if AST or ALT increases by greater than or equal to 50%  relative to baseline and lasts ≥1 week | Discontinue and enter Event Monitoring  Initiate systemic steroid treatment (see Section 9.6) | Discontinue and enter Event Monitoring. |
| Immune System Disorders | **Immune-related Adverse Events** | | |
|  | Grade 2 | *Hold until symptoms resolved to ≤Grade 1, initiate systemic steroid (see 9.6). Discontinue if does not resolve to ≤Grade 1 within 12 weeks after last dose administration, and enter Event Monitoring. | Hold until pembrolizumab resumed. Resume at the next lower dose level (if occurs at 140 mg once daily, discontinue).  Discontinue if pembrolizumab is discontinued, and enter Event Monitoring |
|  | Grade ≥3 (except gastrointestinal and endocrine disorders) | Discontinue and enter Event Monitoring  Initiate systemic steroid treatment | Discontinue and enter Event Monitoring |

| **System/Organ/Class (SOC)** | **ADVERSE EVENTS/SYMPTOMS** | **ACTIONS** | |
| --- | --- | --- | --- |
|  |  | **Pembrolizumab** | **Ibrutinib** |
| Infections and | **Infectious Disorders** | | |
| infestations | Grade ≥3 | *Hold  If ibrutinib is held resume if  ≤Grade 1 or baseline | Hold until ≤Grade 1 or  baseline  Resume at the next lower dose level (if occurs at 140 mg once  daily, discontinue). |

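### Table 8.2 gives incompatible instructions for an immune-related Grade ≥3 maculo-papular rash that settles within 72 hours, and for Grade 3 the row followed decides whether the patient counts under the 30% closure rule

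*Protocol*

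**What the plan says.** Section 8.2 of the protocol has a table of actions for adverse events that are at least possibly related to treatment. Two of its rows matter here.

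- **Rash maculo-papular, Grade ≥3** (skin disorders). Pembrolizumab is held: "If resolves to ≤Grade 1 within 72 hours resume treatment". Otherwise: "If not, discontinue and enter Event Monitoring". Ibrutinib is held until pembrolizumab restarts and then resumes one dose level down (at 140 mg it stops). It also stops if pembrolizumab stops.
- **Immune-related Adverse Events** (immune system disorders). The scope of the upper row is "Grade ≥3 (except gastrointestinal and endocrine disorders". The pembrolizumab action is "Discontinue and enter Event Monitoring Initiate systemic steroid treatment". Ibrutinib is stopped as well. There is no route back to treatment.

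The opening of Section 8 requires strict adherence to the table in the first cycle and treats it as guidance after that. Its only rule for competing actions is: "If multiple adverse events are seen, administer dose based on greatest reduction required for any single adverse event observed".

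Section 16.71 has two closure rules. In the first 6 patients, enrolment closes temporarily if 2 have one of a list of related events, which includes Grade 3+ maculo-papular rash. After that, it closes temporarily once at least 30% of those enrolled have a related toxicity from a table. For toxicities that are neither neurologic nor haematologic, the table counts:

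- Grade 3 still above Grade 1 after 14 days;
- any Grade 4;
- "Any toxicity that leads to treatment discontinuation due to toxicity".

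**The concern.** A rash judged immune-related belongs to both rows, because skin is not among the exceptions of the general row. If the rash settles within 72 hours, one row restarts treatment and the other ends it. Two investigators who both follow the protocol could therefore handle the same patient differently.

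Rash is not a marginal toxicity here. The Rationale in Section 1 reports Grade 3 skin rash in both of the first two patients, within a week of the first pembrolizumab dose. Section 16 records that the study was then stopped for toxicity and redesigned.

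The choice of row also feeds into monitoring. The 30% rule counts a toxicity that leads to discontinuation, so the action taken can turn an uncounted event into a counted one.

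**Working it through.** The plan gives no figure for this point, so there is none to reproduce. The check sets the rows side by side and then applies the 30% rule.

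**Step 1. Is there a tie-break?** The greatest-reduction sentence speaks of several adverse events, not of one event that fits two rows. No other text sets an order between rows, and Section 8 does not define immune-related. The Grade ≥3 rows for pneumonitis and kidney injury and the Grade 3 hepatic row all stop both drugs, in agreement with the general row. The rash row does not.

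**Step 2. Does the conflict arise where the table binds?** Section 7 gives the first pembrolizumab dose on Day 8 of a 28-day Cycle 1. A rash within a week of that dose starts between about Day 8 and Day 15, inside Cycle 1.

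**Step 3. Enumerate.** The case is an immune-related maculo-papular rash at least possibly related to treatment, with ibrutinib above 140 mg. The last two columns apply the 30% rule.

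| Grade | Time to ≤Grade 1 | Rash row | Immune-related row | Counted, rash row | Counted, immune-related row |
|---|---|---|---|---|---|
| 3 | ≤72 h | resume | stop | **no** | **yes** |
| 3 | >72 h to 14 d | stop | stop | yes | yes |
| 3 | >14 d | stop | stop | yes | yes |
| 4 | ≤72 h | resume | stop | yes | yes |
| 4 | >72 h to 14 d | stop | stop | yes | yes |
| 4 | >14 d | stop | stop | yes | yes |

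The rows conflict in 2 of 6 cells. The count changes in 1 of 6.

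**Step 4. Threshold.** Closure needs the smallest whole number of patients that is at least 0.30 × n:

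- n = 10: 0.30 × 10 = 3.0, so 3 patients;
- n = 16 (the stated maximum at the MTD): 0.30 × 16 = 4.8, so 5 patients.

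Each patient in the affected cell moves the numerator by one.

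**Step 5. Illustration with assumed rates.** The documents give no rate for the affected cell. Let *b* be the chance that a patient has some other counted toxicity, and *q* the chance of an immune-related Grade 3 rash that settles within 72 hours, independent of the first. The chance that a patient counts is *b* under the rash row and *b* + (1 − *b*)*q* under the immune-related row. With *b* = 0.15 and *q* = 0.10, the second is 0.15 + 0.85 × 0.10 = 0.235. Binomial chance of meeting the threshold at a single look:

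| n | Needed | Rash row, *b* = 0.15 | Immune-related row, *b* = 0.15, *q* = 0.10 | Range, rash row | Range, immune-related row |
|---|---|---|---|---|---|
| 10 | 3 | 0.180 | 0.429 | 0.070 to 0.322 | 0.167 to 0.759 |
| 16 | 5 | 0.079 | 0.316 | 0.017 to 0.202 | 0.070 to 0.739 |

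The ranges cover *b* from 0.10 to 0.20 and *q* from 0.05 to 0.20. They show how sensitive the rule could be and do not predict what this trial would see.

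**The case against.** The best defence is that the table is arranged by organ class and names maculo-papular rash, so a reader would naturally let the specific row prevail over the general one. That reading is reasonable, but the protocol does not state it. The general row lists the categories it excludes, and skin is not one of them.

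A reader might also infer more than the documents support:

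- **That every Grade 3+ rash falls under both rows.** The Rationale says only "We suspect that this is a result of immunomodulation from the combination therapy", about two patients given ibrutinib 560 mg under the initial design. Section 15 and Appendix VI also list rash as a reaction to ibrutinib itself. Only a rash judged immune-related reaches both rows.
- **That every such rash changes the closure count.** Grade 4 counts under either row, and so does any rash not settled by 72 hours. In the first 6 patients, a related Grade 3+ maculo-papular rash counts whatever action is taken.
- **That the first two patients are examples of the problem.** The documents do not say how fast their rashes resolved, and both predate the current design.
- **That the margin is 7 of 23.** This is the threshold only at full enrolment (0.30 × 23 = 6.9), when closing enrolment no longer does anything. The rule is a running percentage.
- **That dose finding is affected.** The DLT definition for rash rests on grade and response to supportive treatment, not on the action in Table 8.2. The MTD rule and the expansion checks after 3 and 6 patients use DLTs.

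Three further points limit the weight. The 30% rule closes enrolment only temporarily. After Cycle 1 the table is guidance, so some variation is intended. Treatment must start at one centre, so the variation would be between investigators more than between sites. None of these removes the conflict in Cycle 1.

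**Conclusion.** The contradiction is real and narrow. It concerns a Grade ≥3 maculo-papular rash that is judged immune-related and reaches Grade 1 or lower within 72 hours. For that rash, Table 8.2 both resumes treatment and stops it, with no stated precedence, and the table is mandatory in Cycle 1.

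The effect on monitoring is narrower still: Grade 3 only, and only under the 30% rule that applies after the first 6 patients. There, each affected patient moves the numerator by one against thresholds such as 3 of 10 or 5 of 16. How often this would happen cannot be derived from the documents.

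The conclusion assumes that discontinuation in Section 16.71 means stopping both drugs. If ibrutinib is already at 140 mg, the rash row stops it while pembrolizumab resumes, and Section 16.71 does not say whether that counts. The point still deserves correction because it concerns the toxicity behind the redesign and the stated rules cannot both be followed.

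**What to change.** Reconcile the two rows in Section 8.2: state which one governs a maculo-papular rash judged immune-related, and say explicitly whether skin is among the exceptions of the immune-related row. In Section 16.71, state how a Grade 3 rash that settles within 72 hours is counted, so that it is treated the same way whatever is done with treatment. The choice between the two clinical instructions belongs to the investigators and the sponsor.

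The cost is wording in two places. No sample size, threshold or analysis changes.
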